#### **INCLUSION CRITERIA for patients:**

- Patients with mild Alzheimer's dementia (independent in basic and instrumental activities of daily living) according to current clinical criteria
- Signed Informed Consent Form
- Age  $\geq 18$  years
- Presence of a caregiver who can assist the patient and has successfully completed the necessary training for device use

#### **EXCLUSION CRITERIA for patients:**

- Individuals unable to provide informed consent
- Presence of fixed electrical stimulators (e.g., pacemakers, nerve stimulators, hearing implants) that may malfunction or be damaged by electrical or magnetic fields
- Presence of certain metallic foreign bodies (e.g., intrauterine devices, shrapnel, some prostheses, screws, and nails) that could move within a magnetic field
- History of epilepsy
- Pregnant women, as the effects of electrical or magnetic stimulation on a developing fetus are unknown

#### **INCLUSION CRITERIA for the caregiver:**

- Signed Informed Consent Form
- Age  $> 18$  years
- Compliance in participating in training on device usage
- Mini-Mental State Examination (MMSE)  $> 27/30$

[figure not shown][figure not shown][figure not shown]

CLINICA NEUROLOGICA - UNIVERSITA' DEGLI STUDI DI BRESCIA  
UO Neurologia 2 - AZIENDA SOCIO SANITARIA TERRITORIALE degli SPEDALI CIVILI DI BRESCIA  
Direttore: [name]

213

214 **EARLY WITHDRAWAL CRITERIA from the study:**

- 215 - Difficulty in managing the device, measured by the procedure failure rate, as  
216 indicated by the reliability code generated by the device after two training  
217 sessions at the center.

218

219 **STUDY DESIGN:** it is a monocentric, interventional, non-pharmacological,  
220 placebo-controlled, randomized, double-blind clinical study, as neither the patients  
221 nor those administering the evaluation tests will be aware of the type of treatment  
222 provided, real tACS or placebo, followed by an open-label phase. The stimulation  
223 equipment will be pre-programmed (real stimulation or placebo) by another operator  
224 who will not administer the stimulation itself or the tests, thus ensuring the  
225 experimental double-blind. Both the operator administering the treatment and the  
226 operator performing the evaluations will be unaware of the type of stimulation  
227 administered.

228 At baseline (T0), at the end of the double-blind phase (T1, 8 weeks), at the end of the  
229 open-label phase (T2, 16 weeks), and after further follow-up (T3, 24 weeks), each  
230 subject will undergo clinical and neuropsychological evaluation, TMS, EEG, and  
231 blood sampling for the assessment of biological markers such as NfL, pTau,  
232 Abeta40/42, and GFAP. The biological samples will then be sent to the Molecular  
233 Markers Laboratory at the IRCCS Istituto Centro San Giovanni di Dio  
234 Fatebenefratelli in Brescia for analysis of biological markers on extracellular vesicles  
235 from plasma or serum.

236 A subgroup of patients will undergo brain MRI (resting state) at baseline (T0) and at  
237 the end of the double-blind phase (T1, 8 weeks).

238 Each subject will then undergo two further follow-up visits with clinical evaluation at  
239 36 weeks (T4) and 72 weeks (T5) from T0.

240

241 **OBJECTIVES:**

- 242 - Primary objectives: evaluate the tolerability and safety of transcranial alternating  
243 current stimulation (tACS) and its effectiveness on dedicated tests (CDR-SB, ADAS-  
244 Cog13, FNAT, ADCS-ADL).  
245 - Secondary objectives: evaluate the effectiveness of tACS on neurophysiological  
246 imaging parameters, markers of neurodegeneration/plasma amyloidosis.

[figure not shown][figure not shown][figure not shown]

CLINICA NEUROLOGICA - UNIVERSITA' DEGLI STUDI DI BRESCIA

UO Neurologia 2 - AZIENDA SOCIO SANITARIA TERRITORIALE degli SPEDALI CIVILI DI BRESCIA

Direttore: [name]

- Exploratory objectives: evaluate clinical and biological markers at baseline (cognitive reserve index questionnaire, ApoE genotype, BDNF) in response to tACS.

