## END POINTS:

- Primary objectives: it is expected that tACS will be well tolerated (% of compliance >50%) and safe (absence of major adverse events) in the studied population. The effectiveness of the treatment will be evaluated on dedicated tests.

- Secondary objectives: the effectiveness of the treatment on imaging parameters will be evaluated. The effectiveness of the treatment on neurophysiological parameters and plasma neurodegeneration/amyloidosis will be evaluated.

- Exploratory objectives: it is expected that certain biological factors at baseline (e.g., ApoE genotype) may modulate the degree of response to tACS and thus predict the degree of clinical response.

**STATISTICAL PLAN:** as an experimental design, we will use a linear mixed-effects model (LME) with TIME (T0, T1, T2, T3) as a within-subject factor and TREATMENT (sham/real vs real/real) as between-subject factors, considering the subject modeled as a random intercept effect.

We performed a power analysis with G\*Power to estimate the sample size, based on some previously published studies (Benussi et al., *Brain Stimul* 2021; Dhaynaut et al., *J Alzheimers Dis* 2022; Zhou et al., *J Neurol Neurosurg Psychiatry* 2021), using methodologies similar to those applied in the study in question. The effect size  $f(V)$  was calculated using the direct method. Taking into account from the aforementioned studies an effect size equal to a partial  $\eta^2$  of 0.080, corresponding to an effect size  $f(V)$  of 0.295, and considering  $\alpha = 0.05$  and power  $(1-\beta) = 0.90$ , the expected sample size is 34 total subjects. Taking into account a possible attrition rate of 50%, appropriate for long-term studies in patients with Alzheimer's disease, who may have poor tolerability to the device, the final required sample size amounts to 50 total subjects (25 per group).

Correlation analyses (Pearson correlations corrected for multiple comparisons with False Discovery Rate) will be used to evaluate the correlations between biological parameters (plasma neurodegeneration markers) and clinical response. For dichotomous measures (ApoE and BDNF genotype), Fisher's exact test will be used.

**ETHICAL CONSIDERATIONS (RISK-BENEFIT):** tACS is a non-invasive, low-cost, and easy-to-implement technique that is gaining increasing popularity and an expanding range of potential therapeutic applications.

[figure not shown][figure not shown][figure not shown]

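### Four unranked primary efficacy tests share one sample size calculation at an undivided alpha of 0.05, with no rule for what counts as success

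*Protocol*

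**What the plan says.** Protocol, OBJECTIVES: the primary objective combines tolerability and safety with efficacy, worded as "current stimulation (tACS) and its effectiveness on dedicated tests", and names CDR-SB, ADAS-Cog13, FNAT and ADCS-ADL. The four tests appear as a plain list, with no lead outcome and no order.

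Protocol, END POINTS: the efficacy part of the primary entry says only "The effectiveness of the treatment will be evaluated on dedicated tests". It gives no test, no time point and no success rule. By contrast, tolerability has a numerical threshold (compliance above 50%) and safety has a criterion (no major adverse events).

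Protocol, STATISTICAL PLAN: one analysis model is given, a "linear mixed-effects model (LME) with TIME (T0, T1, T2, T3) as a within-subject factor", with treatment sequence as the between-subject factor. One power calculation is given. It starts from "an effect size equal to a partial $\eta^2$ of 0.080", drawn from three published studies, takes alpha as 0.05, and states "power $(1-\beta) = 0.90$ , the expected sample size is 34 total subjects", later raised to 50. The outcome it applies to is not named.

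The same section mentions multiplicity once: "Pearson correlations corrected for multiple comparisons with False Discovery Rate", for the relation between biological parameters and clinical response.

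**The concern.** With four primary tests and no success rule, the protocol does not define what a positive efficacy result is. Two readings are open. Under one, any of the four tests at p<0.05 meets the objective, and the overall false-positive rate exceeds the 0.05 used for sizing. Under the other, all four must succeed, and the power of 0.90 for one test overstates the chance of success. The protocol excludes neither, so the choice could be made after the results are seen. The sample size allows for neither reading.

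Naming the primary outcome and sizing the trial for it are decisions this protocol takes itself. A correction added later in a statistical analysis plan would not change the basis on which the trial was sized.

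**Working it through.** **Inputs from the protocol.** Four primary efficacy tests (OBJECTIVES). Alpha 0.05, power 0.90, partial eta squared 0.080, f = 0.295 and 34 subjects before attrition (STATISTICAL PLAN). Two groups, 1:1 (PROCEDURES).

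**Inputs assumed.** The correlation between the four test statistics is not given. It is taken as equal for all pairs and varied from 0 to 0.9. The number of measurements and the within-subject correlation used in G*Power are not given either.

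**Step 1: the plan's figure of 34.** f = sqrt(0.080/0.920) = 0.295, as stated. For a group-by-time interaction with m measurements and within-subject correlation rho, take noncentrality N·m·f²/(1−rho), with m−1 and (N−2)(m−1) degrees of freedom. With m = 2 and rho = 0.5:

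- Noncentrality at N = 34: 34 × 2 × 0.08696 / 0.5 = 11.83, with 1 and 32 degrees of freedom.
- Power at the full alpha of 0.05: 0.915 at N = 34, against 0.898 at N = 32.

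So 34 is the smallest even total that reaches 0.90. These settings are not stated and others change the answer: four measurements give 22 at rho 0.5 and 44 at rho 0. The result shows only that 34 can be obtained as one test at an undivided 0.05. No allowance for four outcomes is visible.

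**Step 2: any one of four counts, either direction.** For independent tests:

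1 − 0.95⁴ = 1 − 0.8145 = 0.185.

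For correlated tests, the chance that at least one of four equicorrelated normal statistics exceeds 1.96 in absolute value was computed.

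**Step 3: any one of four counts, false benefit only.** For independent tests:

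1 − 0.975⁴ = 1 − 0.9037 = 0.096, against 0.025 for a single test.

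| Assumed correlation | At least one two-sided p<0.05 | False benefit only |
|---|---|---|
| 0 | 18.5% | 9.6% |
| 0.3 | 17.4% | 8.7% |
| 0.5 | 15.6% | 7.8% |
| 0.7 | 13.0% | 6.5% |
| 0.8 | 11.4% | 5.7% |
| 0.9 | 9.4% | 4.7% |
| Single test | 5.0% | 2.5% |

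A three-degree-of-freedom interaction test, which suits four time points, gives nearly the same: 18.5% at correlation 0 and 13.5% at 0.7.

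**Step 4: all four must succeed.** The chance of a false overall success cannot exceed 5%. If each test had the planned power of 0.90, the power to win on all four would be 0.90⁴ = 0.656 for independent tests. It could never exceed 0.90.

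**The case against.** The strongest reply is that the statistical analysis plan is not shown and may contain a testing order or a correction. This stands in part: the absence of a named correction method would not be a finding by itself. What remains is fixed in the protocol: an unranked primary set, no success rule, and one sample size calculation at undivided alpha with no outcome attached.

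A second reply is that the error figures are conditional. This also stands. They require that any one success counts, which the protocol does not say, and they depend on correlations it does not give.

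A reader might go further in four ways that the protocol does not support.

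- **That the risk of a false claim of benefit is 13–19%.** That range counts differences in either direction and stops at a correlation of 0.7. For benefit alone the matching range is 6.5–9.6%, against 2.5%.
- **That multiplicity control protects only exploratory analyses.** The corrected correlations concern plasma neurodegeneration markers, and effects on those markers are a secondary objective. The exploratory genotype analyses use Fisher's exact test, and no correction is mentioned for them.
- **That ADCS-ADL cannot show benefit because patients must be "independent in basic and instrumental activities of daily living) according to current clinical criteria".** The protocol gives no scale range, expected baseline score or expected change, so a ceiling cannot be shown from it. Benefit over sham could also appear as less decline.
- **That splitting alpha four ways has a known cost in power.** At 34 subjects and alpha 0.0125, the Step 1 formula gives 0.61 (two measurements, rho 0.3), 0.78 (two, rho 0.5) or 0.95 (four, rho 0.5). The protocol does not say which settings apply.

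**Conclusion.** The point holds in this form: the protocol sets four primary efficacy tests without rank or success rule and sizes the trial on one unnamed test at 0.05. If any one success counts, the two-sided familywise error is 18.5% under independence, about 13% at correlation 0.7 and about 9% at 0.9. It is above 5% throughout the range examined. The ratio to a single test is similar when only false benefit is counted. If all four must succeed, type I error is not inflated, but the stated power of 0.90 no longer describes the chance of a positive trial. The correlations are assumptions. The finding that the success criterion is undefined does not depend on them.

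**What to change.** Name one primary efficacy outcome, assessed at T1 (8 weeks, the end of the double-blind phase, before both groups receive real stimulation), and test it at 0.05. State that the sample size and the partial eta squared of 0.080 apply to that outcome. The protocol does not show which outcome the 0.080 came from, so the sponsor must confirm the match. If it does not match, the calculation has to be redone for the chosen outcome. List the other three tests as key secondary outcomes, in a pre-stated fixed order or by Holm.

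The cost is protocol wording in OBJECTIVES, END POINTS and STATISTICAL PLAN. The primary test keeps the full 0.05, so multiplicity adds no subjects. The downside is that three outcomes lose unconditional primary status.

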## END POINTS:

- Primary objectives: it is expected that tACS will be well tolerated (% of compliance >50%) and safe (absence of major adverse events) in the studied population. The effectiveness of the treatment will be evaluated on dedicated tests.

- Secondary objectives: the effectiveness of the treatment on imaging parameters will be evaluated. The effectiveness of the treatment on neurophysiological parameters and plasma neurodegeneration/amyloidosis will be evaluated.

- Exploratory objectives: it is expected that certain biological factors at baseline (e.g., ApoE genotype) may modulate the degree of response to tACS and thus predict the degree of clinical response.

**STATISTICAL PLAN:** as an experimental design, we will use a linear mixed-effects model (LME) with TIME (T0, T1, T2, T3) as a within-subject factor and TREATMENT (sham/real vs real/real) as between-subject factors, considering the subject modeled as a random intercept effect.

We performed a power analysis with G\*Power to estimate the sample size, based on some previously published studies (Benussi et al., *Brain Stimul* 2021; Dhaynaut et al., *J Alzheimers Dis* 2022; Zhou et al., *J Neurol Neurosurg Psychiatry* 2021), using methodologies similar to those applied in the study in question. The effect size  $f(V)$  was calculated using the direct method. Taking into account from the aforementioned studies an effect size equal to a partial  $\eta^2$  of 0.080, corresponding to an effect size  $f(V)$  of 0.295, and considering  $\alpha = 0.05$  and power  $(1-\beta) = 0.90$ , the expected sample size is 34 total subjects. Taking into account a possible attrition rate of 50%, appropriate for long-term studies in patients with Alzheimer's disease, who may have poor tolerability to the device, the final required sample size amounts to 50 total subjects (25 per group).

Correlation analyses (Pearson correlations corrected for multiple comparisons with False Discovery Rate) will be used to evaluate the correlations between biological parameters (plasma neurodegeneration markers) and clinical response. For dichotomous measures (ApoE and BDNF genotype), Fisher's exact test will be used.

**ETHICAL CONSIDERATIONS (RISK-BENEFIT):** tACS is a non-invasive, low-cost, and easy-to-implement technique that is gaining increasing popularity and an expanding range of potential therapeutic applications.

[figure not shown][figure not shown][figure not shown]

CLINICA NEUROLOGICA - UNIVERSITA' DEGLI STUDI DI BRESCIA  
UO Neurologia 2 - AZIENDA SOCIO SANITARIA TERRITORIALE degli SPEDALI CIVILI DI BRESCIA  
Direttore: [name]

The tACS used in this study (model: REMOTE mini-CT tES; company: Soterix Medical Inc.) is a medical device with CE marking (no. G1 089785 0013 rev. 00). We hypothesize that tACS may have a positive effect on naming performance in patients with neurodegenerative diseases, such as Alzheimer's disease, and that tACS may have a positive effect on the normalization of neurophysiological parameters that are altered in individuals affected by such neurodegenerative diseases, for which no treatment currently exists.

Literature data show that the application of this method, according to the current safety guidelines (Iyer, 2005; Nitsche, 2003; Wassermann 2005; Antal 2017), has minimal side effects, including mild tingling sensations during or after stimulation, moderate fatigue, mild itching at the electrode application sites, mild burning or pain sensations, headache, nervousness, nausea, and the appearance of vesicles at the electrode application sites in rarer cases.

The stimulation performed at home will not expose the patient to a higher risk compared to stimulation in a hospital setting. The device is designed to be used at home and is equipped with all the safety systems to prevent incorrect or potentially dangerous stimulations.

Regarding the TMS technique, it is a non-invasive brain stimulation method that allows the study of neurophysiological parameters, which can provide information on the pathophysiological mechanisms involved in neurodegenerative diseases.

Literature data show that the application of the method according to current safety guidelines has minimal side effects: a certain number of subjects participating in TMS experiments (up to 20%) report headaches or back pain, most likely due to excessive muscle tension and a rigid position of the head and/or neck during TMS application. These effects are temporary and, in most cases, do not require any treatment.

Since TMS produces a magnetic field, individuals with implanted electrical stimulators (e.g., pacemakers, nerve stimulators, cochlear implants) who would not function or could be damaged by the magnetic field cannot participate in the study. Also excluded are individuals with specific metallic foreign bodies (e.g., shrapnel, certain prosthetics, screws, and nails) that could move if placed within the magnetic field. Since the effects of TMS on the developing fetus are not known, pregnant women cannot participate in the study.

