To evaluate the effects on brain transmission and the underlying mechanisms of this modulation, specific intracortical circuits will be investigated using transcranial magnetic stimulation (TMS), which depends on various neurotransmitters. Over the years, numerous TMS protocols have been developed to obtain neurophysiological parameter information for investigating both the pathogenesis and progression of certain neurodegenerative diseases. Cholinergic brain activity will be assessed using the short-latency afferent inhibition (SAI) protocol (Tokimura et al., 2000). Additionally, electroencephalographic modifications and biological parameters will be analyzed.

**OBJECTIVES:** The aim of this study is to evaluate clinical and biological response markers to home-based transcranial alternating current stimulation (tACS) supervised via telemedicine by investigators in patients with Alzheimer's disease (AD).

**PROCEDURES:** Patients followed at the Neurological Clinic, ASST Spedali Civili di Brescia, and the Neurology Unit, G. Giglio Institute Foundation, Cefalù (PA), with an AD diagnosis based on current clinical criteria, will be enrolled and randomized into two groups:

The first group (group 1) will undergo stimulation protocol using tACS (real), while the second group (group 2) will undergo placebo treatment (sham) (double-blind phase), with a real:placebo ratio of 1:1. Both group 1 and group 2 will then follow an open-label phase with real tACS stimulation. The treatment will be administered during the first week in the hospital, and thereafter, it will be provided at home with supervision from one of the experimenters via telemedicine.

During the first week, the patient and caregiver will receive training at the hospital, where staff will explain how to position and use the device. On the first day, staff will show the patient and caregiver the procedures. On the following days, they will let the caregiver manage the device and will provide support during treatment administration in order to enable the caregiver to manage the device independently at home. During this period, the study's medical staff will assess compliance with the correct procedures and, therefore, the caregiver's ability to manage the device independently. At the end of the training procedure, the investigator will assess the

[figure not shown][figure not shown][figure not shown]

CLINICA NEUROLOGICA - UNIVERSITA' DEGLI STUDI DI BRESCIA  

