#### TREATMENT GROUP - GROUP 1:

The treatment group will undergo tACS sessions (real at 3 mA) applied at the cortical level for 60 minutes/day for 8 weeks, 5 days a week (Monday to Friday). The effects of tACS will be assessed both before and after stimulation, specifically evaluating cognitive performance using dedicated tests (i.e., CDR-SB, ADAS-Cog13, FNAT, ADCS-ADL), neurophysiological parameters (SAI using TMS and brain rhythms using electroencephalography [EEG]), and biological parameters (NfL, pTau, Abeta40/42, and GFAP). In a subgroup, effects on brain magnetic resonance imaging (resting state) will also be evaluated. A 6cc blood sample will also be taken to

[figure not shown][figure not shown][figure not shown]

CLINICA NEUROLOGICA - UNIVERSITA' DEGLI STUDI DI BRESCIA

UO Neurologia 2 - AZIENDA SOCIO SANITARIA TERRITORIALE degli SPEDALI CIVILI DI BRESCIA

Direttore: [name]

determine the ApoE and BDNF genotype, subject to the signing of an informed consent form, in order to evaluate any markers of clinical response.

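### The only criterion for the primary safety objective is that no major adverse event occurs; with 25 to 50 patients exposed, a zero count cannot establish safety, and the concurrent sham arm plays no part in it.

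*Protocol*

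**What the plan says.** The Protocol's OBJECTIVES section (after STUDY DESIGN) opens with "Primary objectives: evaluate the tolerability and safety of transcranial alternating" current stimulation, and places efficacy on the cognitive and functional tests beside it. Under END POINTS, the matching entry states what is expected: good tolerability, with a compliance threshold, and that tACS will be "safe (absence of major adverse events) in the studied population". No other safety criterion is given. The term major is not defined, and nothing says over which period events count, whether they must be device-related, or with what they are compared.

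A comparison is available in the design. Patients are randomised "with a real:placebo ratio of 1:1" and the blinded treatment runs "60 minutes/day for 8 weeks, 5 days a week (Monday to Friday". Both groups then receive real stimulation in an open-label phase, with visits continuing to 72 weeks. The STATISTICAL PLAN uses treatment group only as a factor in the linear mixed model and assigns Fisher's exact test to the genotype measures. The sample size starts from "an effect size equal to a partial" eta squared of 0.080, an efficacy input, and ends with "the final required sample size amounts to 50 total subjects (25 per group"). ADVERSE EVENTS MONITORING requires notification to the ethics committee of events induced by the method, but does not tie this to the endpoint.

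**The concern.** A zero-count criterion without a comparator can mislead in two directions. In a small trial, a device that causes a major event in a few percent of patients can easily show none, and the criterion would then be met. In people with dementia, major events also arise from other illness, so a harmless device could miss the criterion if events of any cause count. The randomised sham period is the one part of the trial that can separate device harm from background events, and the criterion does not use it. At stake is the wording of a primary conclusion: calling the device safe would claim more than this number of patients can support.

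**Working it through.** **The plan's own figure.** The safety criterion has no rate, limit or power attached, so there is none to reproduce. The sample size is an efficacy figure and serves here only as the denominator. Its effect size reproduces: f = √(0.080/0.920) = 0.295. The total of 34 is obtained for a group-by-time interaction with two time points and an assumed correlation of 0.5. The Protocol then raises 34 to 50.

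**Inputs.**
- n = 25: real-arm patients in the blinded phase (Protocol, STATISTICAL PLAN).
- n = 50: all patients, if every one reaches the open-label real stimulation (Protocol, PLACEBO GROUP). This is the most favourable number. The Protocol itself allows for a "possible attrition rate of 50"%, so the number ever exposed to real stimulation lies between 25 and 50.
- True or background rate per patient over the counted period: not given in the Protocol. Assumed 1%, 2% and 5%.
- Patients are treated as independent with a common risk.

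**Step 1. What zero events leaves open.** The one-sided 95% upper limit is 1 − 0.05^(1/n).
- n = 25: 1 − 0.05^(1/25) = 11.3% (two-sided, 1 − 0.025^(1/25) = 13.7%).
- n = 50: 1 − 0.05^(1/50) = 5.8% (two-sided 7.1%).
- To exclude a 5% rate, zero events must be seen in n ≥ ln 0.05 / ln 0.95 = 58.4, that is 59 patients. This exceeds the whole trial.

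**Step 2. Chance of zero or of at least one event.** P(0) = (1 − p)^n and P(≥1) = 1 − (1 − p)^n.

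| Rate p | P(0), n = 25 | P(≥1), n = 25 | P(0), n = 50 | P(≥1), n = 50 |
|---|---|---|---|---|
| 1% | 78% | 22% | 61% | 39% |
| 2% | 60% | 40% | 36% | 64% |
| 5% | 28% | 72% | 7.7% | 92% |

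If p is the rate under real stimulation, P(0) is the chance that the criterion is met despite that rate. If p is purely background and events of any cause count, P(≥1) is the chance that a harmless device misses it. For example, 0.95^25 = 0.277 and 1 − 0.98^50 = 0.636.

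**Step 3. What the sham arm can add.** At 25 against 25, 5 events against 0 gives a two-sided Fisher p of 0.0502, and 6 against 0 gives 0.022. Exact power for 5% against 20% is 20%. The comparison is therefore useful as an estimate with an interval, and too weak to serve as a test.

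**The case against.** Four points can be made on the other side.

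1. The sentence states an expectation. The Protocol never says that one event makes tACS unsafe or that none proves it safe. This is true and limits the point. Still, the sentence stands under END POINTS for a primary objective, next to a numerical compliance threshold, and nothing else defines safety.

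2. A reader might infer that one unrelated event, even during sham or at the 72-week visit, defeats the criterion. The text does not support this: it names no window and does not say that sham-period events count. The monitoring section's reference to events induced by the method suggests that device-related events may be meant. If so, the background-illness half weakens considerably, while the zero-event half stands.

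3. A reader might also pair the 28% for 25 patients with the 64% for 50 as properties of one rule. They use different denominators and rates. On 50 patients, a 5% rate meets the criterion 7.7% of the time.

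4. Intervals and tables by arm may be in an analysis plan that is not shown, so their absence from the Protocol is no fault in itself. That stands. The point concerns the criterion the Protocol does state, which such tables would accompany without changing.

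Finally, the sham comparison will be imprecise at this size (Step 3). That is a reason to estimate and report the uncertainty, and does not favour a count with no comparator.

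**Conclusion.** The point holds in a limited form. As worded, the safety criterion cannot support a conclusion that tACS is safe: zero events leaves rates up to 11.3% (25 patients) or 5.8% (50 patients) unexcluded at one-sided 95%. A true 2% rate would go unseen 60% or 36% of the time respectively. These figures need only the stated sample sizes and independence between patients; the 50-patient figures also need every patient to reach the open-label phase.

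The reverse error, a harmless device missing the criterion in 39% to 92% of trials of 50 patients, is conditional. It requires that events of any cause count and rests on assumed risks of 1% to 5%, for which the Protocol gives no source. The Protocol leaves open whether that condition applies, and should settle it. The matter is one of endpoint definition and the strength of the conclusion; the trial's design already contains the control needed.

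**What to change.** Revise the safety entry under END POINTS so that absence of events is no longer the test of safety.

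- Define a major adverse event and state that events of any cause are counted, with attribution recorded separately.
- For T0 to T1, report the proportion of patients with any major adverse event by arm, the real-minus-sham difference with an exact 95% interval, and the real-arm rate with its exact limit. Present this as estimation and not as a significance test.
- Report events during and after open-label real stimulation separately, with the number of patients exposed and an exact limit.
- If none is seen, write that no major event was observed and give the upper limit for the number actually exposed (one-sided 95%: about 11% for 25, about 6% for 50), in place of calling the device safe.

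No extra patients or visits are needed. Events of any cause must be recorded in both arms, which the Protocol's monitoring text does not itself spell out. The price is a more modest safety statement and a wide between-arm interval.

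### The efficacy model leaves the T0 means free to differ by arm and names only a random intercept: precision is lost at the blinded T1 comparison, and visit-specific standard errors rest on an untested equal-correlation assumption

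*Protocol*

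**What the plan says.** The STATISTICAL PLAN (Protocol, under END POINTS) names one efficacy model: a "linear mixed-effects model (LME) with TIME (T0, T1, T2, T3) as a within-subject factor and TREATMENT (sham/real vs real/real) as between-subject factors". The only thing it says about dependence between a patient's visits is "considering the subject modeled as a random intercept effect". It names no random slope, visit-specific variance or residual correlation. T0 appears as a level of the time factor, not as a covariate, and nothing ties the two arms together at T0.

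STUDY DESIGN places T1 at week 8, when blinded treatment closes, T2 at week 16, when open-label treatment closes, and T3 at week 24. PROCEDURES fixes 1:1 randomisation, and both groups receive real stimulation after T1. T1 is therefore the only post-baseline visit at which real and sham are compared under blinding.

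The sample-size text takes a partial eta-squared of 0.080 and describes it as "corresponding to an effect size $f(V)$ of 0.295". With alpha 0.05 and power 0.90, it states that "the expected sample size is 34 total subjects". This is raised to 50 for an anticipated attrition of 50%. No within-subject correlation or standard deviation is given.

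**The concern.** There are two separate issues.

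**Baseline.** Randomisation makes the T0 means equal in expectation. A model that estimates them freely in each arm ignores this, and its T1 effect is the difference between arms in mean change from T0. That subtracts the whole baseline value where regression would subtract only the predictive part. The cost is precision on the one blinded comparison, in a trial of 50 patients that allows for heavy dropout.

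**Covariance.** A random intercept with independent, equal-variance residuals gives every visit the same variance and every pair of visits the same correlation, whether 8 or 24 weeks apart. With complete data, every arm contrast of change from T0 then gets the same standard error. In a progressive dementia with a treatment switch at 8 weeks this is a doubtful default. If it is wrong, the visit-specific tests are mis-calibrated, and the plan gives no means of knowing in which direction.

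**Working it through.** **Inputs from the protocol:** visits at 0, 8, 16 and 24 weeks; two arms, 1:1; f = 0.295; alpha 0.05; power 0.90; 34 patients before and 50 after attrition; 50% attrition. **Assumed, because the protocol gives none:** all correlations and variances below. I also assume that the model includes the TIME × TREATMENT interaction, which the text implies but does not spell out.

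**1. The plan's own figure.** √(0.080/0.920) = 0.2949, which agrees with 0.295. The total of 34 is reproduced by the repeated-measures interaction test with λ = f²·N·m/(1−ρ), m = 2 measurements and ρ = 0.5 (neither is stated): λ = 0.295² × 34 × 2/0.5 = 11.84 on 1 and 32 df, power 0.916. At N = 32 the power is 0.898, so 34 is the smallest even total. With m = 4 the same formula gives 22.

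**2. Cost of the free T0 means.** For common variance σ² and T0–T1 correlation r, the per-patient variances are:
- change score: 2σ²(1−r)
- adjusted for T0: σ²(1−r²)
- ratio: (1+r)/2

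| assumed r | ratio | variance saved |
|---|---|---|
| 0.5 | 0.75 | 25% |
| 0.7 | 0.85 | 15% |
| 0.85 | 0.925 | 7.5% |

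At r = 0.5, the value that reproduces 34, λ becomes 11.84/0.75 = 15.78. Power at 34 patients rises from 0.916 to 0.970; alternatively 26 patients give 0.914.

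**3. Standard errors under a random intercept.** With complete data, the model's variance for any change contrast is 2 × (mean variance − mean covariance over the four visits). The true value is C₀₀ + Cₜₜ − 2C₀ₜ.

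*AR(1), 0.85 per 8 weeks.* Mean correlation = (3 × 0.85 + 2 × 0.7225 + 0.6141)/6 = 0.768. Model: 2 × (1 − 0.768) = 0.464. True: 0.300 at T1 and 0.772 at T3. SE ratios: √(0.464/0.300) = 1.24 and √(0.464/0.772) = 0.78.

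*Mild random slope* (intercept variance 0.75, slope variance 0.04 per 8-week step, residual 0.25; T0 correlations 0.74, 0.70, 0.64). The squared deviations of 0, 1, 2, 3 from their mean sum to 5, so the model value is 2 × (0.25 + 0.04 × 5/3) = 0.633. True: 0.04 + 0.50 = 0.540 at T1 and 0.36 + 0.50 = 0.860 at T3. Ratios: 1.08 and 0.86.

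*Equal correlation.* Ratio 1.00 at every visit.

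*T0-to-later 0.70, later-to-later 0.85.* Mean correlation 0.775. Model 0.450, true 0.600. Ratio √0.75 = 0.87 at T1, T2 and T3.

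**4. Consequences for tests.** Under AR(1) 0.85, a T1 contrast with 80% power against its true SE has Φ(2.80 − 1.96 × 1.243) = 64% with the model's SE. Its simulated type I error is 1.6%, against 12.9% for a single T3 contrast (25 per arm, complete data). The mild random slope gives 3.5% and 9.1%. The last pattern in step 3 gives 9.2% at T1. The omnibus TIME × TREATMENT test stays between 5.1% and 6.9% in the decay and slope scenarios simulated.

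Mixed-model fits at AR(1) 0.8 with 50% random dropout keep the same direction: SE ratios 1.17 at T1 and 0.75 at T3.

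**The case against.** The strongest reply is that the covariance argument rests on a pattern the protocol never states. A reader might infer that the T1 standard error is certainly too large and the T3 one certainly too small. The document does not support that: equal correlation gives no error, and the last pattern in step 3 reverses the sign at T1. That pattern is not far-fetched, because T0 is the only visit before any stimulation. This objection stands, so the directions are conditional.

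A reader might also take 13% or 9% as the trial's false-positive rate. Those figures belong to a single T3 contrast that the plan does not name; the omnibus interaction test is close to nominal. This stands too.

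Nor is baseline information thrown away. T0 is in the model and the change score uses it, without bias. The loss is one of efficiency. The 25% saving also cannot be combined with the 0.85 decay scenario, where the saving is 7.5%; in the random-slope scenario it is about 12% (adjusted variance 1.04 − 0.75² = 0.4775, against 0.540).

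Finally, residual structure, degrees of freedom and fallbacks are often left to an analysis plan, and one could add a residual correlation to the random intercept. That is fair for detail the protocol omits. It does not answer the points the protocol does fix: T0 as an outcome level with no constraint, and the random intercept as the only dependence named.

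**Conclusion.** The point holds in conditional form, as an improvement worth making and not as an error that invalidates the analysis.

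The baseline part is the firmer. It needs only randomisation and a positive T0–T1 correlation below 1, and no decay pattern. Its size is a T1 variance factor of (1+r)/2 under equal variances, a saving of 7.5% to 25% for assumed r from 0.85 to 0.5.

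The covariance part depends on unknown correlations. Under decay or varying slopes, the T1 standard error is 8% to 24% too large and the T3 one 14% to 22% too small in the two worked examples. Under equal correlation nothing is wrong. If T0 correlates less with later visits than they do with each other, T1 can be anti-conservative. What can be said without assumptions is that the named structure makes visit-specific inference depend on something the trial has not established. With complete data the change-score estimates themselves do not move; only their standard errors and tests do.

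**What to change.** In the STATISTICAL PLAN, make two changes:

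- **Baseline.** Either keep T0 as an outcome and constrain its mean to be common to both arms, or use T0 as a covariate with T1, T2 and T3 as outcomes. Keep the T1 difference as the blinded real-versus-sham contrast.
- **Covariance.** Replace the random-intercept-only structure with an unstructured covariance and Kenward-Roger degrees of freedom. State in advance a simpler structure, such as heterogeneous Toeplitz, to be used if the fit does not converge.

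The cost is wording and minor programming. The statistical price is up to ten covariance parameters for four visits (4 × 5/2), or six if T0 is a covariate (3 × 4/2). If attrition nears 50%, only about 25 of 50 patients would have complete data, so the covariance may be poorly estimated or the fit may fail. That is why the fallback must be fixed beforehand. If correlation is in fact equal across visits, the covariance change costs little and the baseline gain remains.
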